### Sample Size and Data Collection

Patients eligible according to aforementioned inclusion criteria will be selected at the cardiology consultation level or during cardiology or emergency hospitalization. As much as 250 cardiologists (from both public and liberal sectors) will participate in patient selection. Patient inclusion will occur consecutively until the end of the inclusion period. Suitable patients will be selected and requested to sign an informed consent form, confirming their agreement to participate in the study. A detailed questionnaire will then be administered to eligible patients and clinical, biological, and exploratory data will be collected.

The inclusion began on October 2, 2017 (duration 1 month). A regular follow-up was done, wherein patients must visit the cardiology clinic 1, 3, and 12 months after inclusion into the study. This follow-up is provided by the investigator.

Given the observational nature of the NATURE-HF study, no specific treatment or intervention is planned for the management of HF. Patients should be cared for according to the usual medical procedures.

All data are collected via the DACIMA Clinical Suite web interface [8]. The platform complies with international standards FDA 21 CFR part 11 (Food and Drug Administration 21 Code of Federal Regulations part 11), HIPPA (Health Insurance Portability and Accountability Act), ICH (International Conference on Harmonisation), MedDRA (Medical Dictionary for Regulatory Activities), Health Canada, and Tunisian regulations.

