### Statistical Analysis

The DACIMA Clinical Suite platform enables the collection of online data and their extraction in SAS or SPSS format. Statistical analysis will be performed with SAS software (University Edition; SAS Institute). The statistical analysis is exploratory, involving the calculation of 95% CI.

The data will be described for the whole analyzed population. Continuous quantitative variables (eg, age, weight, left ventricular ejection fraction, biological parameters) will be described by the number of patients documented, mean, median, SD, and extreme values. Categorical variables will be described by the number and percentage of each category.

The normality of the continuous quantitative variables will be verified with the Shapiro–Wilk test. If the hypothesis of normality is rejected, then a simple transformation will be made on the variable to normalize it. If this transformation succeeds in normalizing the variable, then the analysis will be performed on the transformed variable. Otherwise nonparametric tests will be used or possibly an analysis on the quartiles or quintiles will be performed.

Statistical tests will be bilateral with a statistically significant threshold of 5%. An analysis of variance will be performed for the quantitative variables (parametric test for the variables that follow a normal distribution, and nonparametric test in other cases) and a chi-square test will be realized for the categorical variables. The Yates correction or Fisher exact test will be used if the validity conditions for the chi-square test are not met (theoretical number <5).

The sample size (both power and sample) is estimated by the SPSS 2008 software (IBM). To estimate the number of patients to be included in this study, a range of 95% CI (5% significance threshold) is set as the primary endpoint. The impact of this criterion is estimated at 35%, based on the US registry OPTIMIZE-HF [9], which found a hospital mortality ranging from 2.2% to 4.1%, a global mortality ranging between 6.5% and 9.1%, and an overall incidence of all events evaluated (rehospitalization or death) ranging from 35.3% to 36.6%.

Considering these data, the number of patients to be included in the study would be 1436. However, by predicting a 5% missing data rate and a 10% loss to follow-up, the sample size to be selected will be 1700 patients.

The intermediate analyses will be carried out after formulating the statistical analysis plan.

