## Results

A total of 95 cardiologists included 1700 patients in the registry with a 1-year follow-up period. All patients provided written informed consent. Patients were officially enrolled in NATURE-HF only if they were aged 20 years or older.

The NATURE-HF registry does not impose any specific intervention. Treatment of patients follows the usual recommendations for the management of HF. Clinical events occurring during the follow-up will be collected in order to evaluate the judgment criteria planned in the protocol. However, at the end of the study, a detailed report of the clinical events will be prepared by the STCCCV (Société Tunisienne De Cardiologie Et De Chirurgie Cardiovasculaire [Tunisian Society of Cardiology and Cardiovascular Surgery]) and the document provided to the National Center for Pharmaco-Vigilance.

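### The sample size shows no allowance for clustering by recruiting cardiologist, and the named tests assume independent patients, although 95 cardiologists enrolled all 1700

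*Protocol article*

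**What the plan says.** All references are to the protocol article.

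- **Basis of the sample size (Statistical Analysis).** The size rests on an interval: "a range of 95% CI (5% significance threshold) is set as the primary endpoint". The expected rate is given as "The impact of this criterion is estimated at 35" percent, taken from a US registry with "an overall incidence of all events evaluated (rehospitalization or death) ranging from 35.3% to 36.6" percent. The result is "Considering these data, the number of patients to be included in the study would be 1436". A 5% missing-data rate and a 10% loss to follow-up are the only reasons given for raising this to 1700. No target width, design effect or ICC is stated.
- **Analysis (Statistical Analysis).** "The statistical analysis is exploratory, involving the calculation of 95% CI". The section names ANOVA or a nonparametric test for quantitative variables, and chi-square, Yates or Fisher for categorical ones. All are two-sided: "Statistical tests will be bilateral with a statistically significant threshold of 5" percent. It does not say how the CIs are computed.
- **Recruiters planned (Sample Size and Data Collection).** "As much as 250 cardiologists (from both public and liberal sectors) will participate in patient selection".
- **Recruiters obtained (Results).** "A total of 95 cardiologists included 1700 patients in the registry with a 1-year follow-up period".
- **Why patients of one cardiologist may be alike.** Diagnosis is left to the investigator (Study Design and Patient Enrollment). Care follows usual practice, and the investigator provides the follow-up (Sample Size and Data Collection). One secondary endpoint is physicians' adherence to European recommendations (Registry Objectives).

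**The concern.** Patients who share a cardiologist share that doctor's case mix, diagnostic threshold, treatment habits and follow-up. Their outcomes are therefore likely to be positively correlated, and 1700 such patients carry less information than 1700 independent ones. A sample size and tests built on independence then overstate precision: nominal 95% intervals cover less than 95%, and tests on factors that vary mainly between cardiologists reject too often.

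The penalty grows with cluster size, and the mean cluster is about 2.6 times what 250 recruiters would have given. The adherence endpoint is the most exposed, because it measures what the physician does.

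**Working it through.** **1. Reproduce 1436.** Inputs from Statistical Analysis: p = 0.35, two-sided 95%. The width is not given and has to be inferred.

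- Normal approximation, assuming half-width 2.5 points: n = 1.96² × 0.35 × 0.65 / 0.025² = 1398.3, so 1399. With continuity correction: 1438.
- Exact (Clopper-Pearson) total width at p = 0.35: 5.0012 points at n = 1435 and 4.9995 at n = 1436. This matches 1436, but it uses a fractional event count (0.35 × 1436 = 502.6). With 503 events the width is 5.0004.
- Working back from 1436 by the normal formula: 1.96 × √(0.2275/1436) = 2.47 points.

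So 1436 fits a CI about 5 points wide with independent patients. The fit supports that reading but does not prove it.

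**2. Is there room for a design effect in 1700?** 1436/0.85 = 1690, and 1436/(0.95 × 0.90) = 1680. The stated allowances leave 10 to 20 patients. A design effect of only 1.05 would need 1436 × 1.05/0.855 = 1764 patients or more. None is included.

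**3. Cluster size.** 1700/250 = 6.8 as planned; 1700/95 = 17.9 as obtained. With 15% attrition, 1700 × 0.85 = 1445 are evaluable, so m = 1445/95 = 15.2.

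**4. Effect of clustering.** The ICC is assumed over a range and clusters are taken as equal.

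- Design effect: DE = 1 + (m − 1) × ICC
- Effective n = 1445/DE
- Half-width = 1.96 × √(0.2275 × DE/1445)
- Coverage of an unadjusted interval = 2Φ(1.96/√DE) − 1

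| Assumed ICC | DE | Effective n | Half-width (points) | Unadjusted coverage |
|---|---|---|---|---|
| 0 | 1.00 | 1445 | 2.46 | 95% |
| 0.005 | 1.07 | 1349 | 2.55 | 94.2% |
| 0.01 | 1.14 | 1265 | 2.63 | 93.3% |
| 0.02 | 1.28 | 1125 | 2.79 | 91.6% |
| 0.05 | 1.71 | 845 | 3.22 | 86.6% |
| 0.10 | 2.42 | 597 | 3.83 | 79.2% |

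Example at ICC 0.05: DE = 1 + 14.21 × 0.05 = 1.71, and 1.96 × √(0.2275 × 1.71/1445) = 3.22 points.

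**5. Sensitivity.**

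- Unequal clusters, DE = 1 + ((1 + CV²)m − 1) × ICC. At an assumed CV of 0.8 and ICC 0.05: DE 2.20, half-width 3.6 points, coverage 81%.
- All 1700 evaluable (m = 17.9), ICC 0.01: DE 1.17, effective n 1454, still above 1436.
- 250 cardiologists, 1445 evaluable (m = 5.8): DE 1.05 at ICC 0.01 and 1.24 at ICC 0.05, with half-widths of 2.52 and 2.74 points.

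**The case against.** The strongest reply has four parts.

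- **The CI method is unknown.** A reader might infer that every 95% CI will treat patients as independent. The document does not say so. It names no CI method, and Data Review refers to a final statistical analysis plan that is not shown and could contain cluster-robust or mixed-model intervals. This stands, so the finding on CIs is conditional. It does not cover the named tests, which in their standard form assume independence, or the sample size, which visibly contains no allowance.
- **No precision target is stated.** A reader might infer that the planned precision is not delivered. That cannot be shown: the 5-point width is back-solved, the ICC is unknown, and at ICC 0.01 with every patient evaluable the effective n still exceeds 1436. This stands.
- **The 95 is a recruitment result.** With 250 cardiologists the allowance would have been small, so the realised count does not show that the calculation was wrong when made. This also stands, but the analysis has to suit the sample obtained.
- **Little depends on it.** The analysis is declared exploratory, and 2.6 to 3.2 points instead of 2.5 is unlikely to change a conclusion about a 35% rate. That limits the severity. In addition, no comparison of public with private sector is planned, so inflated error for that contrast cannot be charged to the plan.

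**Conclusion.** The point holds in conditional form. The sample size makes no visible allowance for clustering by cardiologist, and the named tests do not fit patients recruited, treated and followed by 95 doctors. If the analyses stay unadjusted, intervals for the primary endpoint will be too narrow: slightly at ICC 0.01 (2.6 points, about 93% coverage), materially at ICC 0.05 (3.2 points, about 87%).

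These figures assume 1445 evaluable patients, equal clusters, a 35% rate and ICC values that the document does not supply; unequal clusters would make them worse. For physician adherence the loss is likely larger: an assumed ICC of 0.10 gives a design effect of 2.4. That value is an illustration, not a figure from the document.

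This is a should-fix point. The harm depends on an unknown ICC, and no confirmatory claim rests on these intervals.

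**What to change.** 1. State that CIs and tests use cluster-robust variance (survey-type or GEE with sandwich errors) or a random intercept, with the recruiting cardiologist as the cluster, in place of unadjusted ANOVA and chi-square tests.
2. Report the estimated ICC and the distribution of patients per cardiologist, at least for the primary endpoint and for adherence.
3. State the CI width behind 1436, and give the expected half-width as about 2.6 to 3.2 points for ICC 0.01 to 0.05.

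The cost is some wording in the analysis plan, which the Data Review Committee is already charged with validating, and a cardiologist identifier that the registry should already hold. No further enrolment is needed. The downside is somewhat wider reported intervals.

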### Data Review

The Data Review Committee includes the Coordinators of the Steering Committee of the study as well as the scientific team of DACIMA Consulting. The purpose of the Data Review Committee is to respond to specific queries in data management, and to validate the statistical procedures developed in the final statistical analysis plan. The Data Review Committee will also be responsible for validating subsequent publications.

### Expected Implications

The NATURE-HF is the first large-scale investigation to clarify the contemporary demographic data, management, and outcomes of patients with HF.

### Oversight and Leadership

The protocol of the NATURE-HF registry has been approved by the Tunisian Society of Cardiology and Cardiovascular Surgery. The NATURE-HF study has been registered in ClinicalTrials.gov (trial registration number NCT03262675).

## Results

A total of 95 cardiologists included 1700 patients in the registry with a 1-year follow-up period. All patients provided written informed consent. Patients were officially enrolled in NATURE-HF only if they were aged 20 years or older.

The NATURE-HF registry does not impose any specific intervention. Treatment of patients follows the usual recommendations for the management of HF. Clinical events occurring during the follow-up will be collected in order to evaluate the judgment criteria planned in the protocol. However, at the end of the study, a detailed report of the clinical events will be prepared by the STCCCV (Société Tunisienne De Cardiologie Et De Chirurgie Cardiovasculaire [Tunisian Society of Cardiology and Cardiovascular Surgery]) and the document provided to the National Center for Pharmaco-Vigilance.

## Discussion

HF is a major health concern worldwide and one of the most important causes of hospitalization [10]. Acute HF is responsible for over 1 million hospitalizations each year in the United States, with a similar number also being reported in Europe [11]. These hospitalizations are responsible for an increased economic burden and are associated with high mortality rates, up to 20% in the 6 months following hospital discharge [12]. HF management is challenging given the heterogeneity of the patient population, absence of an universally accepted definition, incomplete understanding of its pathophysiology, and lack of evidence-based guidelines. Most patients appear to respond well to initial therapies consisting of loop diuretics and vasoactive agents [13,14]. However, these treatments fail to decrease postdischarge mortality and re-admission rates. In the last few years, many drugs have been evaluated to treat HF; unfortunately, results were disappointing in terms of efficacy and safety [15-22].

This large, contemporary longitudinal study of Tunisian patients with HF will provide a unique opportunity to answer many clinical questions. The NATURE-HF study is important in several respects. First, systematic observational and outcomes data can be generated from this registry study, which is especially valuable given that previous data for Tunisian patients with HF are limited. Second, treatment of HF changes dramatically, and thus HF management needs to be evaluated in real-world studies. Third, the NATURE-HF study provides a good opportunity to compare treatment and response variation among HF populations in Africa for comparison with different countries and evaluate adherence to recent guidelines.

The NATURE-HF study will fill a significant gap in the dynamic landscape of HF care and research. It will provide unique and necessary data on the management and outcomes of patients with HF. This study will yield the largest contemporary longitudinal cohort of patients with HF in Tunisia.

## Abbreviations

FDA: Food and Drug Administration
HF: heart failure
HIPPA: Health Insurance Portability and Accountability Act
ICH: International Conference on Harmonisation
MedDRA: Medical Dictionary for Regulatory Activities
STCCCV: Société Tunisienne De Cardiologie Et De Chirurgie Cardiovasculaire (Tunisian Society of Cardiology and Cardiovascular Surgery)
